### **The Cloud DX Kit**

The technology we will use in the study is the Cloud DX Connected Health Kit. All patients will be provided with the Cloud DX Connected Health Kit as a tool for self-monitoring and asynchronous remote monitoring. It consists of a custom Tablet computer, Pulsewave® wrist cuff monitor (Health Canada license, Appendix 2), Oximeter (Health Canada license, Appendix 3), Scale and Thermometer (Health Canada license, Appendix 4). Cloud DX is also a licensed distributor of medical devices (MDEL: 6984, Appendix 5). Patients are also provided with a comprehensive user manual (Appendix 6). All of these devices are optimized to work together, pre-paired and ready to go out of the box. All patients will use the kit to record daily their physiological and symptom readings. All patients will also answer general questions about their symptoms, by filling out a digital version of the COPD Assessment Test (CAT, Appendix 7) (Jones et al., 2009) and MRC scale (Stenton, 2008) (Appendix 8). The Pulsewave wrist cuff measures blood pressure, heart rate, breathing rate and detects cardiac anomalies with comfort and ease of use.

All patients in the RM and SM group will also be provided with an action plan document that will be given on a piece of paper. This document consists of a chart that instructs patients on what to do if their readings fall outside their respirologist pre-specified values. The action plan includes actions such as calling the clinic, filling out a prescription or going to the emergency department (see Appendix 17).

For patients assigned to the RM group, if a patient's readings fall outside the pre-determined thresholds, a notification will be sent to the clinical project specialist at MSH and to the patient through email notifying them that the reading exceeded the threshold. Patients in the RM group will also receive a follow-up call from the clinical project specialist whenever their readings exceed thresholds. The follow-up calls will be done only Monday to Friday 9-5. An attempt to complete the follow-up call will be done within 24 hours of receiving the notification and a message will be left to call back the clinical project specialist if patients are not available when that call is made. The purpose of the call is to check on the patients, to encourage them to follow their action plan and to use the call as an educational opportunity to teach patients about

COPD as their questions arise. Patients in the RM group will also have the option to send a message to the clinic with any non-emergency questions they may have.

Notifications in the SM group will be recorded and sent to the clinic, but their notifications will not be actively monitored or acted upon.

Aside from these regular (primary) notifications, all patients (both SM and RM group) will have a secondary threshold levels preset by their respirologist for oxygen levels, heart rate and blood pressure. These will be extreme measures that require immediate assistance. Cloud DX staff will monitor these levels (as they normally currently do and are required by Health Canada regulations). In the event that a patient exceeds a secondary threshold, they will be contacted by Cloud DX, to ensure that everything is ok and advised to contact 911. All of these events will be communicated back to the clinical project specialist. Cloud DX monitors these readings Mon-Friday 830am-800pm and weekends and holidays 9am-1 pm.

All patients will be advised to go to the emergency department as they would normally if they feel they have the need to. Patients will also be informed that data is not monitored 24hrs/7 days a week and if they need care immediately to respond to their clinical needs as they would normally do outside of the study.

All physiological and symptom recordings taken by the patients will be transmitted to a secure Web site where they can be accessed by a pre-determined set of the patient's clinical care providers. The clinical project specialist at MSH will monitor each patient's recordings once a week and receive notifications when a patient's readings exceed the specific thresholds. The employee will screen any notifications or messages received once a day Mon-Fri. Each patient will have a personalized threshold level for their vitals that will be based on a threshold predetermined by the respirologist. The clinical project specialist monitoring the data for the RM group can access the data by looking at the Clinician Dashboard in this central web portal, accessible on any PC, Mac or mobile device. By monitoring blood pressure, pulse oxygen, temperature and body weight and using smart surveys, clinicians at MSH will have a better idea of the level of control each patient has over their COPD; which patients need the most help adjusting to their COPD management plan at home; and which COPD patients need to be seen in a community setting, maximizing scarce resources. Patients in the RM and SM groups will be instructed to refer to their action plan with each reading and follow the flow chart based on their symptoms and readings. The data of the patients in the RM group will also be screened at the clinic once a week, even if no notifications have been sent. Patients will be informed that their data will not be screened constantly and if they feel unwell, they should contact their clinical provider as they would do normally or go to the emergency room if they feel they need to see a doctor immediately or if the clinic is closed. Participants who have not entered data for a week will also be contacted by the clinical project specialist to inquire whether there is still interest in participation.

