## **2. Research Objectives**

Therefore, the goal of the current project is to investigate the effectiveness of implementing a technology-enabled self-monitoring program (SM group) or a technology enabled self- and remote-monitoring program (RM group) in a COPD patient population compared to standard of care. Effectiveness will be measures by outcomes examining patients' self-management skills, quality of life, COPD knowledge and respiratory symptoms. The standard of care group (SC group) currently does not use any technology to monitor patients at their home. Therefore the following 3 conditions will exist in the study:

1. SM group: Patients in this group will be recording their vitals and symptoms with the Cloud DX platform everyday and will be provided with an action-plan that instructs them on what to do in response to their readings.
2. RM group: Patients in this group will be recording their vitals and symptoms with the Cloud DX platform everyday and will be provided with an action-plan that instructs them on what to do in response to their readings. In addition, a respiratory therapist (RT) will be monitoring asynchronously their vitals and contacting them when their vitals exceed pre-determined thresholds. The RT will also check on patients once a week irrespective of the value of the vitals.

3. SC group: patients will not be provided with a technology or an action plan (as the action plan is based on vitals and symptoms).

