#### d. Intervention

Patients will be randomized to either SM, RM group or SC group (41 patients per group). Patients in the SM and RM group will receive the Cloud DX kit at the start of the trial and will continue using it for 6 months. Patients in the SC group will be given the opportunity to receive the kit at the end of the trial and use it for free for 6 months (see Figure 1). All patients will complete 3 assessments: at baseline, 3 months and 6 months on a series of questionnaires (see Outcome section for a list and description). They will also complete a demographic questionnaire at the initial visit (Appendix 13). The clinical project specialist at MSH will be responsible for collecting all data at each visit. The initial visit is expected to take 2 hours, allowing for obtaining consent, an introduction of the kit, and survey completion. Subsequent visits are expected to take about 1 hour to complete, as only surveys will be filled out. Visit 2 and 3 will be done in-person or remotely as surveys will be completed through REDCap and patients will have the option to complete them online from their home or over the phone. The clinical project specialist will make contact with the patient via telephone to remind them of the survey deadline. If patients prefer to come in person, they will be provided with that option. If the patient prefers to conduct the survey over the phone, they will be transferred over to the research team at WCH with a script (Appendix 20). Once the patient verbally agrees, the clinical project specialist at MSH will call one of the Research Assistants at WCH to provide the patient name, telephone number, and email address (if applicable). If the Research Assistant does not pick up, a voice message will be left on the Research Assistant's password protected mailbox. The Research Assistant then documents patient information in a password protected Excel document in the WCH internal drive. The Research Assistant will then contact the patient to conduct the survey as well as email the patient for any follow-up requests from the phone call, ie. to resend the REDCap survey link.

Patients in the SM and RM group will also be contacted by the clinical project specialist 2 weeks after receiving their kit to review whether their thresholds have been set properly. If a revision of the thresholds is needed this will be done with the respirologist's approval.

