## **Data collection, management, and statistical analysis**

All quantitative continuous data will be analysed by conducting a between-group repeated-measures ANOVA analyses comparing the scores at baseline, 3m and 6m follow-up assessments of each group. We will also run within-group comparisons, examining differences in performance between each assessment at baseline, 3m and 6m follow-up. All analysis will be run by a statistician at WIHV.

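### The call after a week without kit data asks SM and RM patients, but never SC patients, whether they still want to take part, which risks adherence-related attrition in the two kit arms only

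*Protocol*

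**What the plan says.** The rule is at the end of The Cloud DX Kit, in Protocol section 4.d. Anyone who goes seven days without sending readings is to be "contacted by the clinical project specialist to inquire whether there is still interest in participation". The trigger is missing kit data, and the question put is about taking part.

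Section 2 describes the control arm: "SC group: patients will not be provided with a technology or an action plan". Section 4.d adds that "Patients in the SC group will be given the opportunity to receive the kit at the end of the trial", that is, after the 6-month comparison.

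One sentence under The Cloud DX Kit reads differently: "All patients will use the kit to record daily their physiological and symptom readings". Taken literally it includes SC. It conflicts with the two statements above, and the passages need to be reconciled.

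On follow-up, section 4.d says "All patients will complete 3 assessments: at baseline, 3 months and 6 months on a series of questionnaires". No condition of kit use is attached. The 3- and 6-month surveys may be done online, by telephone or in person, with a telephone reminder of the deadline.

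The analysis paragraph names a between-group repeated-measures ANOVA "comparing the scores at baseline, 3m and 6m follow-up assessments of each group". It states no rule for patients who lack a 6-month score.

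**The concern.** Stopping the intervention and leaving the study are different events. A patient who stops taking readings can still fill in the PIH at 6 months, and that score belongs in the comparison of randomised arms. This call responds to the first event by asking about the second, and the protocol does not say that a patient who stops the kit stays in follow-up.

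The prompt is also one-sided. It reaches poor adherers in SM and RM, while comparable patients in SC are never singled out and asked. The PIH covers skills in monitoring and responding to symptoms, so a patient who has stopped daily monitoring may plausibly score lower on it. If such patients leave the kit arms and their counterparts stay in SC, the patients left in the kit arms are a favourable selection. Scores that were never collected cannot be fully recovered by analysis, least of all when the reason for leaving is tied to the outcome.

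**Working it through.** **Who can trigger the call.** The trigger needs kit data. SM and RM have the kit for 6 months; SC has none until the trial ends. The trigger can therefore operate only in SM and RM. The post-baseline study contact described for all arms is the survey reminder, which does not ask about leaving.

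**The plan's own figures.** Inputs from section 4.f: 41 per group, effect 0.42 (PIH) and 0.27 in absolute value (SGRQ), correlation 0.85, α = 0.05.
- SD of change, in baseline SDs: √(2 × (1 − 0.85)) = 0.548.
- Standard error, 41 v 41: 0.548 × √(2/41) = 0.121.
- One-sided power (normal approximation): 0.966 for PIH and 0.721 for SGRQ, against the stated 0.97 and 0.71. A two-sided test gives 0.935 and 0.607, which do not match. Sidedness is not stated; that is a separate matter.

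**Is it a power problem?** Losing 20% of one kit arm leaves 41 × 0.8 = 32.8 patients. The standard error becomes 0.548 × √(1/32.8 + 1/41) = 0.128, and one-sided PIH power falls only from 0.966 to 0.948. The issue is selection, not power.

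**Size of the possible bias.** Three assumptions are needed, none of them in the protocol: a share q of a kit arm leaves without a 6-month PIH, nobody leaves SC by a similar route, and leavers' mean PIH change is g baseline SDs below that of stayers.
- If stayers' mean change is S, the full-arm mean is (1 − q)S + q(S − g) = S − qg.
- An analysis of stayers alone estimates S, so its bias is q × g.
- Type I error below is two-sided at nominal 0.05, for no true effect in the full arms, from bias divided by standard error (normal approximation).

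| q | g (SD) | Bias (SD) | Share of 0.42 | Type I error |
|---|---|---|---|---|
| any | 0 | 0 | 0% | 0.050 |
| 0.05 | 0.25 | 0.013 | 3% | 0.051 |
| 0.10 | 0.25 | 0.025 | 6% | 0.055 |
| 0.10 | 0.50 | 0.050 | 12% | 0.069 |
| 0.20 | 0.25 | 0.050 | 12% | 0.068 |
| 0.20 | 0.50 | 0.100 | 24% | 0.122 |

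Example, last row: 0.20 × 0.50 = 0.10; 0.10/0.42 = 24%; 0.10/0.128 = 0.78 standard errors.

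The bias is zero in every row if leavers still give a 6-month PIH. If SC lost the same share of similar patients, its own q × g would cancel it.

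**The case against.** The strongest reply is that the protocol sets no withdrawal rule. The specialist only asks. Such a call could just as well bring a silent patient back and improve retention. All patients are due the surveys at 3 and 6 months whatever their kit use, by whichever route suits them. The ANOVA is named without a complete-case rule, and handling of missing scores is ordinarily left to a statistical analysis plan, which is not shown. Patients in any arm may stop: the Risks section says that participation is voluntary and gives anyone who feels upset the option to stop.

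Most of this stands. A reader might infer that the call does bias the PIH comparison. The document does not support that. Bias needs three links that it does not establish: that the call makes patients leave who would otherwise have stayed, that those patients give no 6-month PIH, and that the analysis then leaves them out.

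A reader might also infer that the call contaminates SM by adding staff contact. That is not supported either. SM already has a specialist contact at 2 weeks to review thresholds, and calls from Cloud DX when a secondary threshold is exceeded, so it was never contact-free.

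What the reply does not remove is the wording. The stated purpose of the call is interest in taking part, not help with the kit. The survey schedule does not say what happens to a patient who answers no. Only the kit arms are asked. This is a rule of trial conduct, not a gap that an analysis plan would be expected to fill.

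**Conclusion.** The point holds as a risk, not as a demonstrated bias. The protocol contains a prompt to consider leaving that is triggered by poor adherence and can occur in only two of three arms, in an open-label trial with a self-reported self-management outcome. The likely direction, if non-users manage themselves less well, favours SM and RM over SC.

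The size cannot be determined from the document. Over the illustrative range of up to 20% leaving and a deficit of up to 0.5 SD, the bias is 0 to about 0.1 SD, at most about a quarter of the planned 0.42. That rests on assumed values for both quantities, on no comparable loss from SC and on leavers giving no 6-month PIH. It is a cheap improvement worth making, and no ground for saying that the randomised comparison is broken.

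**What to change.** In the paragraph on participants without data for a week (The Cloud DX Kit, section 4.d), and in any script for the call:
- Make the purpose a check on kit use and technical problems.
- State that stopping the kit is not withdrawal from the study.
- Say explicitly that the 3- and 6-month surveys in section 4.d are still sought from patients who stop readings.
- Record stopping the kit and withdrawing from follow-up as separate items, each with a date, so that both can be shown by arm.

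At the same time, reconcile the sentence that has all patients using the kit with the description of SC.

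The cost is one or two sentences in the protocol and script and an extra REDCap field. Remote surveys are already provided for, so keeping non-users in follow-up is feasible. The downside is that the estimated effect may be smaller because non-users stay in.

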#### e. Outcomes

##### i. Primary Outcome

- *The Partners in Health (PIH) scale* (Petkov, Harvey, & Battersby, 2010) (Appendix 9). A validated scale measuring the current status of self-management, with items on knowledge of the condition and skills to monitor and respond to symptoms.

##### ii. Secondary Outcomes

- Quality of Life and Respiratory symptoms will be assessed with the *St. George's Respiratory Questionnaire (SGRQ)* (Jones, Quirk, & Baveystock, 1991) (Appendix 10).

The St. George's Respiratory Questionnaire (SGRQ) is an index designed to measure and quantify health-related health status in patients with chronic airflow limitation. It has been shown to correlate well with established measures of symptom level, disease activity and disability. The first part ("Symptoms") evaluates symptomatology, including frequency of cough, sputum production, wheeze, breathlessness and the duration and frequency of attacks of breathlessness or wheeze. The second part has two components: "Activity" and "Impacts". The "Activity" section addresses activities that cause breathlessness or are limited because of breathlessness. The "Impacts" section covers a range of factors including influence on employment, being in control of health, panic, stigmatization, the need for medication, side effects of prescribed therapies, expectations for health and disturbances of daily life.

- Bristol COPD Knowledge Questionnaire (White, Walker, Roberts, Kalisky, & White, 2006) (Appendix 18) is a measurement of COPD patients' disease knowledge level. It consists of 13 subscales, each of which assesses a topic of COPD knowledge: (1) epidemiology, (2) aetiology, (3) symptom, (4) breathlessness, (5) phlegm, (6) infections, (7) exercise, (8) smoking, (9) vaccination, (10) inhaled bronchodilators, (11) antibiotics, (12) oral steroids, and (13) inhaled steroids. This test has been used in the past to assess patients' knowledge of COPD (Choi, Chung, & Han, 2014; Zhang et al., 2014).
- The COPD Assessment Test (Jones et al., 2009) (Appendix 7)
- MRC Breathlessness Scale (Stenton, 2008) (Appendix 8)
- Patients will also be asked to self-report at baseline, 3m and 6m the following measures for the past 3 months: the number of ED presentations, number of admissions to a hospital, the length of stay for all admissions (in days), number of exacerbations (episodes in which antibiotics or steroids were prescribed or hospital/clinic visit due to a respiratory issue), number of visits to family doctor, number of nurse contacts, self-reported use of medication, self-reported smoking cessation (Appendix 13)
- Number of contacts/calls to the outpatient clinic and deaths will also be kept track of by the clinical project specialist at MSH

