### **4. Methods**

#### **a. Study Setting**

The study will be conducted at Markham Stouffville Hospital (MSH) with most patients being recruited from the Outpatient COPD Clinic (Respiratory Health-COPD Clinic). Recruitment will be coordinated internally by the clinical project specialist, who is also a respiratory therapist. Some patients will also be identified through inpatient admission records and the Health for All Family Health Team (FHT) by their family doctors who have clients that are living in the community with diagnosed COPD. Additional patients will be recruited by respirologists. These respirologists practice at the Outpatient COPD clinic, but also have separate private practices in Markham. Finally, patients will be recruited from the Outpatient COPD Exercise Rehabilitation Program that is run at the Cornell Community Centre in collaboration with MSH. These patients will be approached by an MSH respiratory therapist who coordinates the rehabilitation program. We have already established a research collaboration with the hospital during the design phase of this project that informed our methods and recruitment practices. Access to potential patients will be determined locally, in-house at MSH by the clinical project specialist, who is also a respiratory therapist. All data collection will be done internally at MSH. All initial contact will be done internally to the site from where the patient is originating (e.g. Outpatient COPD Clinic, COPD rehabilitation program, Family Health Team (FHT), or a respirologists' private practice). For sites that are outside MSH, patients will be provided with the brochure for the study and will be asked for permission to be contacted by the clinical project specialist.

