#### **c. Recruitment**

Recruitment will be on-going until 123 patients have been recruited for the intervention phase (see sample size justification in Section 6.b). Patients will be approached by the clinical staff (respirologist or respiratory therapist-RT) who will introduce the technology to them and provide them with brief information about the trial with a brochure (Appendix 19) and request permission to pass the patient's information to the clinical project specialist at MSH. At this time the consent

form will also be given to give the patients enough time to consider participation. The clinical project specialist will later call the participants to further inquire about their interest in participating and to provide further details about the project. At this time they will also confirm the patient has a copy of the consent form and if they don't have the clinical project specialist will email it to the patient. The patients who are still interested in the project will be scheduled for their baseline evaluation, at which time informed consent will be signed (Appendix 1) and the Cloud DX kit will be provided to them. Patients can split that session into two, if they feel it is too much for one visit. There will also be a recruitment video that will be uploaded on YouTube. The clinical project specialist will email the link with the brochure to interested patients. The clinical project specialist will also be showing the video on a tablet to patients in the Outpatient COPD Exercise Rehabilitation Program. The Inpatient RT will show the video on a tablet to patients with COPD prior to their discharge from hospitalization.

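### The baseline 3-month utilisation count can include the admission through which a patient was recruited, which biases the within-group comparisons with 3m and 6m towards a fall; the randomised comparison is not biased

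*Protocol*

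**What the plan says.** Four parts of the protocol bear on this.

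- **Recruitment.** Section 4.a says most patients come from the outpatient clinic ("with most patients being recruited from the Outpatient COPD Clinic"), but adds: "Some patients will also be identified through inpatient admission records". Section 4.c adds a ward route: "The Inpatient RT will show the video on a tablet to patients with COPD prior to their discharge from hospitalization".
- **Timing of entry.** Section 4.b requires no period free of admissions or exacerbations. Section 4.c gives no interval between discharge and the baseline visit: "The patients who are still interested in the project will be scheduled for their baseline evaluation".
- **Utilisation outcomes.** Section 4.e.ii sets the same look-back at all three assessments: "Patients will also be asked to self-report at baseline, 3m and 6m the following measures for the past 3 months". The items include ED presentations, admissions, length of stay and "number of exacerbations (episodes in which antibiotics or steroids were prescribed or hospital/clinic visit due to a respiratory issue"). No rule excludes the admission that led to recruitment.
- **Analysis.** The statistical analysis paragraph first names a between-group method ("All quantitative continuous data will be analysed by conducting a between-group repeated-measures ANOVA analyses"). It continues: "We will also run within-group comparisons, examining differences in performance between each assessment at baseline, 3m and 6m follow-up".

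**The concern.** A patient who enters the trial by way of an admission, and has the baseline visit within 3 months of it, must report at least one admission with its bed-days. If that admission was respiratory, it also meets the protocol's definition of an exacerbation. Nothing requires an event in the 3m or 6m window. The baseline window is thus partly filled by the selection of patients, while the follow-up windows are filled only by the ongoing event rate. Comparing them within an arm mixes this selection effect with any effect of the programme.

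What is at stake is how before-after figures in the SM and RM arms would be read. The Study Significance section hopes that both programmes will lead to fewer outpatient and inpatient visits. A within-arm fall in admissions would look like that benefit, yet an inert kit would tend to produce it too.

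**Working it through.** The protocol states no admission rate and no share recruited through an admission, so it has no figure of its own to reproduce here. Its power figures concern PIH and SGRQ, and this point does not rest on them.

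**Inputs**

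- From the protocol: 41 patients per arm, alpha 0.05, and a 3-month look-back at each assessment.
- Assumed: *p*, the share of an arm whose recruiting admission falls inside the baseline window, and λ, the ongoing number of admissions per patient per 3 months, taken as the same before and after entry. Shares of 5%, 10% and 20% correspond to about 2, 4 and 8 of 41 patients.

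**Expected counts with no programme effect**

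- Baseline mean = λ + *p*; follow-up mean = λ.
- Proportional fall = *p* / (λ + *p*).
- Example: λ = 0.2 and *p* = 0.10 give 0.30 at baseline and 0.20 at follow-up, a fall of 0.10/0.30 = 33%.

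**Chance of a significant within-arm fall.** Simulation with 10,000 runs and 41 patients per arm. Counts are Poisson with gamma-distributed patient rates (shape 1). At baseline, one admission is added for a share *p* of patients. The test is a paired t-test at two-sided 5%, counting only significant falls, so the nominal figure is 2.5%.

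| *p* | λ | Baseline mean | Follow-up mean | Expected fall | Significant fall in an arm |
|---|---|---|---|---|---|
| 0 | 0.1 | 0.10 | 0.10 | 0% | 2.2% |
| 5% | 0.1 | 0.15 | 0.10 | 33% | 8.0% |
| 10% | 0.1 | 0.20 | 0.10 | 50% | 20.2% |
| 20% | 0.1 | 0.30 | 0.10 | 67% | 55.4% |
| 0 | 0.2 | 0.20 | 0.20 | 0% | 2.2% |
| 5% | 0.2 | 0.25 | 0.20 | 20% | 6.6% |
| 10% | 0.2 | 0.30 | 0.20 | 33% | 15.1% |
| 20% | 0.2 | 0.40 | 0.20 | 50% | 40.1% |

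The rows with *p* = 0 also show what happens if the recruiting admission is left out of the baseline count: the expected change is zero and the error is close to nominal.

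**Sensitivity to the constant-rate assumption.** Suppose 20% of an arm is recruited through an admission and has an ongoing rate of 0.5, while the rest have 0.1. Baseline mean = 0.2 × (1 + 0.5) + 0.8 × 0.1 = 0.38. Follow-up mean = 0.2 × 0.5 + 0.8 × 0.1 = 0.18. The fall is 0.20/0.38 = 53%, compared with 67% when everyone has rate 0.1.

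**Between-arm comparison.** In the same simulations, extended to *p* from 0 to 50% and λ from 0.1 to 0.4, a two-arm comparison of change rejects 4.6-5.3% of the time. It keeps its 5% level.

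**The case against.** The strongest reply is that the trial is randomised and its objective is comparison with standard care. Recruitment route precedes allocation, so the artefact is shared across arms in expectation, and a similar fall in the SC arm would expose it. This stands. It confines the problem to the within-group comparisons.

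The outcomes are also secondary. Section 2 defines effectiveness by self-management, quality of life, knowledge and symptoms, and the primary outcome is not a utilisation count. The analysis paragraph speaks of continuous data and of performance, so applying the within-group step to counts is a reading of the text. It is a natural one, since the counts are collected at the same three assessments and no other analysis is named for them.

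Several stronger readings are tempting, but the documents do not support them.

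- *Every arm is bound to show a fall.* The bias is an expectation. Over λ = 0.1-0.4, all three arms show an observed fall in 22-33% of simulated trials at *p* = 5%, 39-63% at 10% and 71-94% at 20%. Most patients come from the outpatient clinic, the admission records carry no recency limit, and the baseline date after discharge is not given.
- *The recruiting admission normally brings an ED visit and an exacerbation with it.* The ward route covers inpatients with COPD, not only those admitted for it, and nothing is said about how they were admitted.
- *Post-discharge recovery inflates improvement in SGRQ, CAT and MRC.* This would depend on an interval that the protocol does not state, and no size can be put on it.
- *A recruiting clinic visit fills the baseline exacerbation count in the same way.* The definition is loose enough to invite this, but clinic visits can also occur in follow-up, so the same one-sided floor is not shown.

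Finally, Appendices 21 and 22 (chart review) are not shown and may already record admissions. That would help to identify the recruiting admission, but it would not change the self-reported baseline count.

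**Conclusion.** The concern holds for the within-group comparisons of admissions and bed-days, and of exacerbations where the recruiting admission was respiratory. In expectation these comparisons are biased towards a fall in each arm with no programme effect. The direction follows from the recruitment routes, the absence of an admission-free period and the look-back rule.

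The size does not follow from the text. It depends on the unstated share enrolled within 3 months of a recruiting admission and on the ongoing rate. For assumed shares of 5-20% and rates of 0.1-0.2 per 3 months, the expected fall in admissions is about 20-67%, with a significant within-arm fall in about 7-55% of arms. Higher rates in recently admitted patients bring these figures down.

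The randomised comparison between arms and the PIH result are not biased, so this is a worthwhile, inexpensive correction to secondary analyses and no threat to the trial's main conclusion.

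**What to change.** In section 4.e.ii and the statistical analysis paragraph:

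- Define admissions, bed-days, ED visits and exacerbations as post-randomisation counts over months 0-6 (the 3m and 6m reports together cover this period), compared between arms, with the baseline 3-month count as a covariate only.
- Drop the within-group before-after tests for these items. If a before-after figure is shown descriptively, leave the recruiting admission out of the baseline count.
- Record at enrolment the recruitment source and whether an admission led to it, so that this admission can be identified.

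There is also a gain in precision compared with analysing change from baseline. Under the model above, the variance of the change score is 2λ + *p*(1 − *p*). At λ = 0.2 and *p* = 0.20 the recruiting admission raises it from 0.40 to 0.40 + 0.16 = 0.56. Using follow-up counts as the outcome removes that added noise.

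The cost is some wording and one REDCap field, with no change to sample size or visits. The drawback is that the before-after utilisation figures are lost or become less favourable.
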